### Intervention

Matching of participants into dyads will be conducted by a research coordinator based on evidence-informed criteria developed in our formative study [50]. For participants to be matched, they must: (1) live in the same time zone, (2) be in the same age range (i.e., within ± 10 years of age), and (3) self-report similar current exercise volume (i.e., within 30 min per week). Beyond these core matching criteria, we will create discrepancy scores based on other personal and cancer-related characteristics, such as cancer stage at diagnosis, treatment status, time since treatment, participants’ family situation (e.g., having a romantic partner and/or children), and exercise preferences (e.g., preferred time of day for exercise) [25, 51] and account for discrepancies in these characteristics in analyses. All participants will receive an ‘Exercise Peer Support Guide’ that provides tips and strategies for supporting their exercise peer [52, 53] and a one-page infographic highlighting current exercise guidelines for cancer survivors [16–18]. All participants will be given a Fitbit wearable activity tracking device, which will be used for device-measured MVPA. Matched exercise peers will be introduced to one another by a research assistant via Zoom (video conferencing platform) prior to the start of the study period. Refer to Fig. 2 for a study flow chart.

#### Intervention condition

Participants in the *MatchQEP* group will receive exercise information and program sessions tailored by a QEP specifically for each BCS in the dyad. A single QEP, with advanced training on exercise for individuals with cancer, will provide all QEP sessions for each dyad. The study QEP also has research experience leading longitudinal and experimental trials while also holding a PhD in behavioral medicine. *MatchQEP* dyads will meet with the QEP via Zoom once per week for 10 weeks. Each weekly session will last up to 60 min and will include a review of the exercise program, achievement of goals/action plans set, adverse effects/events, and discussion on overcoming barriers to completing the prescribed exercise program. The actual length of the session, in minutes, will be noted. Additionally, the QEP will follow a standardized guide to deliver specific sessions each week based on behavior change counselling support strategies [54, 55] (see “Appendix”). Based on current exercise recommendations for cancer survivors [16–18], the overall goal of the QEP-prescribed exercise intervention is for each member of the dyad to complete a minimum of 150 min of MVPA per week, which may include both aerobic and resistance forms. Consistent with home-based exercise strategies, the QEP will tailor the program based on personal circumstances, including cancer-related characteristics, side effects, current fitness level, and available space and equipment [16]. *MatchQEP* group participants will have the opportunity to reach out to the QEP individually if they need to ask specific and personal questions during the intervention period. For 4 weeks following the completion of the 10-week intervention, the QEP will be available for consultation (i.e., a post-intervention tapering period) as needed by the *MatchQEP* group participants. This tapering period is important for understanding strategies to successfully taper BCS from exercise trials. All interactions between the QEP and the dyads from intervention initiation until the end of the tapering period will be recorded.

#### Control condition

BCS in the *Match* (control) group will independently communicate and support each other around exercise for 10 weeks. They will not have any contact with a QEP during this time and will structure their own communication with their matched peer. After the 12 weeks post-intervention follow-up assessment (26 weeks post-baseline), BCS in this group will be offered a single consultation session with a QEP to discuss exercise-related questions.

### Data collection and measures

Following informed consent, all BCS will complete a demographics questionnaire, including questions related to peer matching criteria, treatment, and exercise history. To determine the effectiveness of the intervention, BCS will complete exercise volume, social support, and HRQOL questionnaires online at four time points: baseline, post 10-week intervention, post 4-week tapering (i.e., 14 weeks post-baseline), and at 12 weeks post-intervention follow-up (i.e., 26 weeks post-baseline). BCS will be asked to wear the Fitbit to collect device-measured MVPA for one week at all four timepoints. Self-reported sedentary behavior will be assessed as a potential covariate at all time points. The QEP alliance (i.e., connection to the QEP support provider) will be assessed as a covariate at post-intervention and post-tapering time points. Adherence to the intervention will be calculated at the end of the intervention period (10 weeks) and cost-effectiveness will be assessed at post-intervention (10 weeks), post-tapering (14 weeks), and at the 12-week post-intervention follow-up (26 weeks after baseline assessment).

### Primary outcome

Exercise volume at the post 10-week intervention time point, will be measured using a valid and reliable self-report survey (modified Godin Leisure Time Exercise Questionnaire) [56–58]. The modified Godin Leisure Time Exercise Questionnaire is a self-report measure which asks respondents to give weekly frequencies and durations of strenuous, moderate, and mild aerobic activities. Resistance training volume will also be self-reported using the same format as the aerobic activities (e.g., frequency and time metrics). Responses on moderate and strenuous activities are summed to determine total MVPA volume. This measure will also be assessed at the post-tapering (i.e., 14-weeks) and 12 weeks post-intervention follow-up (i.e., 26 weeks post-baseline) time points.

### Secondary outcomes

Device-measured MVPA, social support, and HRQOL are secondary outcomes.

#### Device-measured MVPA

Exercise volume will also be assessed using a tracking device (Fitbit Inspire® 2 accelerometer). Adherence to Fitbit’s use in cancer survivors is high [59, 60] and Fitbit exercise data has demonstrated high correlation to Actigraph measures in this population [59]. Fitbit devices will be mailed to BCS at study inception and will be required to be worn for 7 consecutive days during the four primary data collections to determine their average daily and weekly 

s of MVPA and step count. BCS are not required to wear the device outside of the data collection timeframes, but can wear them if they choose. Total wear time and corresponding data will be collected by a research assistant via the online Fitbit database in each participants unique, deidentified study Fitbit account and will be used to characterize the use of Fitbit devices over the entire study duration. Participants will keep the devices post-intervention.

#### Social support

A breast cancer-specific version of the Social Support Survey (SSS) [31, 61, 62] will be used to assess seven dimensions of social support: listening support, task challenge, emotional support, esteem support, reality confirmation, tangible assistance, and understanding breast cancer support [31, 61, 62]. Within each dimension, respondents will be asked to score two questions on a five-point Likert scale (amount (total number) and satisfaction with each type of support rated from very dissatisfied to very satisfied). The SSS has demonstrated adequate construct validity in sport settings [57] and has been validated in a sample of BCS [63]. Participants will also rate the amount (total number) and perceived quality (from very dissatisfied to very satisfied) of support they receive in the following exercise-related support categories: listening support, task challenge, emotional support, esteem support, reality confirmation, tangible assistance, and informational support. At the post-intervention, post-tapering, and follow-up assessments, participants will rate, on a seven-point scale ranging from 1 (none at all) to 7 (a lot), the amount of each type of exercise-related support that they received from their study exercise partner since the last assessment time. For the purpose of this study, a total social support latent variable will be estimated to account for general and exercise-specific social support. See Additional file 1.

#### HRQOL

The Short-Form-12 (SF-12) [64, 65] and the EQ-5D-3L [66] will be used to assess HRQOL. The SF-12 is a self-administered questionnaire consisting of 12 items addressing eight domains of health (physical functioning, role-physical, bodily pain, general health, vitality, social functioning, role-emotional, and mental health). The SF-12 has demonstrated validity in adult populations when compared to the SF-36, with high correlations for both the physical (*r* = 0.94–0.96) and mental (*r* = 0.94–0.97) domains, showing that it is a practical alternative to the longer SF-36 [65]. The EQ-5D-3L [66] is a two-part measure. The first part using a three-level scale to assess five dimensions of health (mobility, self-care, usual activities, pain/discomfort, and anxiety/depression). The second part assesses responder’s perception of their health on a visual analogue scale from 0 (worst imaginable health) to 10 (best imaginable health). This measure is reliable and valid for individuals with cancer [67]. For the purpose of this study, a total latent variable for HRQOL will be tested and used in the main analysis exploring HRQOL effects as a secondary outcome of the study.

### Tertiary outcomes

#### Intervention adherence

The QEP will track *MatchQEP* group adherence by completing a weekly session log. The QEP will record attendance of each BCS at the virtual QEP session as well as whether each individual completed the goals set from the previous session. *MatchQEP* group adherence is defined as the number of sessions attended divided by the total number of sessions. Adherence in the *Match* group will be determined by the number of times the peers connect during the 10-week intervention period.

#### Cost-effectiveness

The costs of the *MatchQEP* intervention will be calculated and compared to traditional face-to-face costs of QEP services in Canada and to the *Match* group alone. Refer to Table 2 for a description of costs to be compared between *MatchQEP* group and traditional QEP services. The use of health care resources will also be compared between the two groups at the post-intervention, post-tapering, and follow-up time points using a piloted questionnaire [68] that assesses health care facility visits, doctor visits, procedures received, support services used, and loss of work (see Additional file 2).

**Table 2 Tab2:** Cost of *MatchQEP* group versus traditional QEP services

*MatchQEP group*		
Program costs^#^	Professional time/labor	# of contact hours × unit cost of Qualified Exercise Professional (QEP) over the 10-week intervention period and 4-week tapering period*
	Equipment	Any device a survivor may purchase (pay out of pocket) for use at home based on the QEP’s recommendation (such as TheraBand or free weights) Computer for QEP
*Traditional QEP services*		
Session costs^#^	Total cost of QEP session	Includes venue use/cost of membership, equipment at venue, preparation time for the QEP
	Labor	# of QEP sessions attended during a comparable 10-week period × cost of each session
Travel	Mileage estimates	Based on distance (km) from an individual’s home to the session venue and the cost of gas (/km)
	Public transportation costs	
	Parking costs	
Home-based equipment		Any form of device that a survivor may purchase for use at home based on the QEP’s recommendations (for example, TheraBand or free weights)
Consumable materials	Photocopies of home exercises	
	Printed letters/folders given to survivors	

^*^For each 1-h contact cost, 1.5 h of labor will be allocated to account for the preparation time required for each session

^#^The cost of training staff will be excluded as staff will already be qualified for their role

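### For MatchQEP versus traditional QEP services, Table 2 counts MatchQEP labour over 14 weeks against 10 and omits matching and introduction labour, so the cost comparison is not like for like

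*Protocol article*

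**What the plan says.** The Cost-effectiveness section under Tertiary outcomes plans two comparisons: MatchQEP with traditional face-to-face QEP services, and MatchQEP with Match. Table 2 serves the first ("Refer to Table 2 for a description of costs to be compared between" MatchQEP and traditional services).

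- **MatchQEP labour:** contact hours times the QEP's unit cost, "over the 10-week intervention period and 4-week tapering period". A footnote to that row adds preparation: "For each 1-h contact cost, 1.5 h of labor will be allocated to account for the preparation time required for each session".
- **Traditional labour:** the number "of QEP sessions attended during a comparable 10-week period", times the cost of each session.
- **Other MatchQEP rows:** equipment only, namely home devices bought on the QEP's advice and a computer for the QEP.
- **Other traditional rows:** venue, equipment and preparation within the session cost, then travel, parking, home equipment, photocopies and printed material.
- **Stated exclusion:** one only. "The cost of training staff will be excluded as staff will already be qualified for their role".

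The Intervention section describes two staff tasks that have no row in Table 2: "Matching of participants into dyads will be conducted by a research coordinator", and "Matched exercise peers will be introduced to one another by a research assistant via Zoom".

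**The concern.** The Study purpose section expects MatchQEP to have lower direct costs than traditional in-person and clinical services, and the Statistical analysis section makes that direct-cost comparison the test. A difference between two totals answers the question only if both cover the same period and each includes the labour its service needs. Here the table describes the traditional window as comparable while the MatchQEP window is four weeks longer. One column also leaves out labour that is specific to a peer-matched programme and that the article does not describe for in-person services.

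The two faults act in opposite directions, but nothing in the article suggests that they are of equal size, so they cannot be assumed to cancel. The Discussion intends the result for health-care policy makers choosing how to deliver exercise services, who would take the difference at face value.

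**Working it through.** The article gives no cost total, unit cost, tapering hours or matching hours, so there is no planned figure to reproduce. The check has two parts: set the rows side by side, then see how large each gap could be in labour hours.

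**Side by side (Table 2)**

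| Item | MatchQEP | Traditional |
|---|---|---|
| QEP labour window | 10 + 4 = 14 weeks | 10 weeks |
| QEP preparation time | counted (footnote) | counted (in session cost) |
| Dyad matching by coordinator | no row | no such step described |
| Zoom introduction by assistant | no row | no such step described |

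**Documented inputs**

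- Ten weekly sessions per dyad; "Each weekly session will last up to 60 min" (Intervention condition).
- 1.5 h of labour for each contact hour (Table 2 footnote), read as 1.5 h in total, preparation included. The footnote is attached to the row that covers both periods, so it applies to tapering contact too.
- Tapering contact is as needed, with no fixed number of hours (Intervention condition).

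**Ten-week QEP labour, maximum**

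10 sessions × 1 h × 1.5 = 15 h per dyad, or 15 / 2 = 7.5 h per woman.

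**Window gap.** Assume 0 to 4 contact hours per dyad in tapering; the upper end is one hour in each of the four weeks.

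- Lower: 0 × 1.5 = 0 h, or 0%.
- One hour in all: 1 × 1.5 = 1.5 h; 1.5 / 15 = 10%.
- Upper: 4 × 1.5 = 6 h; 6 / 15 = 40%.

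Table 2 charges this to MatchQEP, with no equivalent period in the traditional column.

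**Omitted labour.** Assume 0.5 to 4 staff hours per dyad for matching and introduction together.

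- Lower: 0.5 / 15 = 3%.
- Upper: 4 / 15 = 27%.

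These are hours, not dollars. Coordinator or assistant time may be paid differently from QEP time.

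**Both corrected.** Compare 10-week labour plus matching with the labour that Table 2 would count as written.

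- Most tapering, least matching: (15 + 0.5) / (15 + 6) − 1 = 15.5 / 21 − 1 = −26%.
- No tapering, most matching: (15 + 4) / 15 − 1 = 19 / 15 − 1 = +27%.

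The sign changes within the assumed ranges, so the article does not fix the direction of the net error.

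**The case against.** The strongest reply is that the table is a reasonable scope choice in a condensed article. Several parts of that reply stand.

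- **Tapering belongs to MatchQEP.** Leaving it out would understate the programme's cost, and counting it works against the sponsor's own hypothesis. That is right. The fault is only that the headline comparison sets 14 weeks against 10. Extending the traditional column to 14 weeks would not repair this, because it would set four more weeks of sessions against as-needed consultation.
- **The data for a 10-week figure are already planned.** Cost-effectiveness is to be assessed at 10 and 14 weeks (Data collection and measures), and all QEP interactions are recorded to the end of tapering (Intervention condition). This is also right. It makes the change cheap, but Table 2 still specifies a single labour row covering both periods.
- **Matching happens in both arms.** It therefore cancels in MatchQEP versus Match, the randomised comparison behind the incremental ratios. A reader might infer that the omission distorts that comparison as well; it does not. It does not cancel against traditional services.
- **Travel and parking appear only in the traditional column.** This is no inconsistency, since virtual delivery does not incur them.
- **The article may leave costing detail to a fuller document.** That would cover a silent article. This one prints both windows and the cost rows, and its only stated exclusion is staff training.

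A reader might also infer that the Fitbit is a missing MatchQEP cost. The documents do not support that. Both arms receive it, it serves device-measured MVPA, and wear is required only in the four data-collection weeks. It is a measurement cost of the trial.

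**Conclusion.** The point holds for MatchQEP versus traditional QEP services only. As written, Table 2 compares 14 weeks of QEP labour with 10, and leaves out the matching and introduction labour that the peer programme needs.

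Relative to a documented maximum of 15 h of QEP labour per dyad, the window gap is 0 to 40% and the omission 3 to 27%. Both ranges rest on assumed hours, unweighted for pay rates, and the upper end of the first requires every dyad to use a full hour in each tapering week. Neither is set against a traditional-service cost, because the article gives none.

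It would be tempting to conclude that the plan favours MatchQEP, or that it penalises it. With a possible net change of −26% to +27%, neither conclusion is supported. Severity is minor: the outcome is tertiary, and the primary and secondary analyses are untouched.

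**What to change.** Three edits to Table 2:

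1. Make the 10-week cost the like-for-like comparison with traditional services.
2. Move the 4-week tapering contact to its own line, and give a 14-week MatchQEP programme total beneath it.
3. Add a MatchQEP row for staff time spent on matching and on the Zoom introduction.

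Do not add a Fitbit row.

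The first two edits need no new data. The third needs existing staff to log their time per dyad as the work is done, since it is hard to reconstruct later. Dyads are matched before they are allocated, so the log should cover all 54 planned dyads, and the average can be applied to the MatchQEP column. The cost is minor logging and a MatchQEP figure that may prove less favourable. Design, sample size and treatment do not change.

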### Descriptive data and covariates

Age in years, stage of cancer, time since treatment, time since diagnosis, current medications, and exercise preferences will be self-reported at baseline in an online demographic questionnaire. The Sedentary Behavior Questionnaire [69] will be used to assess the amount of time (in hours) per week spent engaged in sedentary pursuits (e.g., watching television, sitting and reading). The scale has demonstrated reliability and validity in adult populations [69]. Sedentary behavior will be a covariate [70]. Exercise peer match quality (assessed on a 5-point scale from 1: very poor match to 5: very good match), amount of time spent with peer, method of connecting with peer, and perceived similarities with peer (assessed on a 5-point scale from not at all similar to extremely similar) will be collected post-intervention and used as covariates in analyses (see Additional file 3). Therapeutic alliance between participants and the QEP will be assessed by each participant in the *MatchQEP* group at the post intervention (10 week) and post tapering (14 week) time points using the modified Work Alliance Inventory—Short Form Revised (WAI-SR) [71]. The WAI-SR is a twelve-item scale evaluating three domains of therapeutic alliance: (1) agreement between patient and therapist on the goals of treatment, (2) agreement between patient and therapist about the tasks to achieve these goals, and (3) the quality of the bond between the patient and therapist (QEP) [71]. Each item is assessed on a 7-point Likert scale from 0 (never) to 7 (always), with higher scores representing higher satisfaction with the therapist (QEP)-patient relationship [65]. The WAI-SR is a reliable and valid outcome for assessing therapeutic alliance (internal consistency: α = 0.91, test–retest reliability: *r* = 0.93; and construct validity: *r* = 0.74) [71].

#### Safety/adverse events

While exercise is known to be safe for BCS when performed correctly [14, 15], minor injuries have the potential to occur in any exercise intervention. To enhance participant safety in this study, all participants will be cleared to exercise prior to enrollment using the PAR-Q+/ePARmed-X+, [72] with physician clearance as needed. For the women in the *MatchQEP* group, tailored exercise recommendations will be provided during the exercise program delivery. Any injuries or side effects that occur in the *MatchQEP* group will be tracked by the QEP on an ‘events’ log with all adverse events classified on severity with specific types/class using the “Common Terminology Criteria for Adverse Events”. Adverse events will be reported to the Principal Investigator immediately for follow-up with BCS and connection to physician for further consultation.

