### Treatment allocation and randomization

Dyads will be randomized (1:1) to the intervention (*MatchQEP*) or control (*Match*) group prior to baseline assessment. Treatment allocation will be centrally randomized using a web-based scheme (https://www.randomizer.org/). The randomization will be completed by a PhD student external to the research team and group allocation will be assigned in the order in which participants have completed an initial background and demographics questionnaire and have been matched with a peer for the study. Although the research coordinator(s), QEPs, and participants cannot be blinded to treatment allocation, the primary investigators and statistician completing data analysis will be blinded.

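### Injuries and side effects are tracked systematically only in MatchQEP, and in neither arm after week 14, so harms in the 54 Match women would be under-recorded and any description of harms by arm distorted

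*Protocol article*

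**What the plan says.** The Safety/adverse events section starts with both arms: every participant is screened for exercise before enrolment, with physician clearance where needed. It then narrows to one arm: "Any injuries or side effects that occur in the *MatchQEP* group will be tracked by the QEP", on an events log graded by CTCAE. It ends with an escalation rule that names no arm: "Adverse events will be reported to the Principal Investigator immediately for follow-up with BCS and connection to physician for further consultation".

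The Intervention condition section shows how events reach the log. The agenda of each weekly session over 10 weeks includes "adverse effects/events, and discussion on overcoming barriers to completing the prescribed exercise program". For 4 further weeks the QEP is available on request, and interactions with the dyads are recorded until the end of that tapering period.

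For the comparator, the Control condition section says: "They will not have any contact with a QEP during this time and will structure their own communication with their matched peer". The one QEP consultation offered to Match women comes after the week-26 assessment.

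Under Treatment allocation and randomization, the article says that "the primary investigators and statistician completing data analysis will be blinded".

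**The concern.** Match is an active comparator. Its women are paired to support each other's exercise and receive a peer support guide, a summary of exercise guidelines and a Fitbit. Eligibility extends to stage IV disease and to any stage of treatment. The safety section itself acknowledges that minor injuries can occur in any exercise intervention. Yet the one mechanism described for finding injuries depends on QEP contact, which Match women do not have.

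Two things are at stake. Harms under peer-only exercise would be under-recorded, although peer matching without a QEP is a model whose wider use the article discusses. And if events are ever described by arm, weekly asking in one arm would be set against spontaneous reporting in the other, which makes QEP support look less safe than it is.

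A smaller, separate matter is that the only described source of event reports is the MatchQEP log. A report reaching the Principal Investigator would therefore usually show that dyad's allocation, which sits awkwardly with the blinding statement.

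**Working it through.** **Women per arm.** The Sample size section gives 43 + 11 = 54 dyads, and 54 × 2 = 108 women, which reproduces the stated total. Randomization is 1:1 by dyad, so each arm has 27 dyads, or 54 women. With the stated 30% attrition, 54 × 0.7 = 37.8, about 38 women.

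**Event capture by period** (periods from Data collection and measures; capture from Intervention condition, Control condition and Safety/adverse events):

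| Period | MatchQEP | Match |
|---|---|---|
| Weeks 0–10 | Asked at each weekly session, logged by the QEP | None described |
| Weeks 10–14 | QEP available on request, contacts recorded | None described |
| Weeks 14–26 | None described | None described |

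**Coverage, before attrition.**
- Planned follow-up: 108 × 26 = 2,808 woman-weeks.
- Scheduled asking: 54 × 10 = 540 woman-weeks, and 540 / 2,808 = 19%.
- Adding the on-request tapering weeks: 54 × 14 = 756, and 756 / 2,808 = 27%.
- Match: 0 of 54 × 26 = 1,404 woman-weeks.

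**Other two-arm data.** The questionnaires named for both arms cover exercise volume, social support and HRQOL, with sedentary behaviour as a covariate. A further questionnaire, used for cost-effectiveness, asks both arms about facility and doctor visits, procedures, support services and loss of work at weeks 10, 14 and 26. As described, none of these records an injury or links a visit to exercise, and an injury that led to no care would be missed by the health care use items.

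**Effect of unequal ascertainment.** Let *p* be a true event rate common to both arms, and *c*₁ and *c*₀ the shares of events captured in MatchQEP and Match. The expected observed difference is *p*(*c*₁ − *c*₀). The article gives no event rates, so take *p* = 10% and *c*₁ = 1 as assumptions:
- *c*₀ = 0: 10% × (1 − 0) = 10 percentage points
- *c*₀ = 0.5: 10% × (1 − 0.5) = 5 percentage points
- *c*₀ = 1: no difference

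The direction is against MatchQEP whenever *c*₀ is below *c*₁. The size cannot be known from the article.

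**What equal capture would give.** If an arm of 54 had no events, the one-sided 95% upper bound on its rate would be 1 − 0.05^(1/54) = 5.4%. With 38 women it is 1 − 0.05^(1/38) = 7.6%. Power to compare arms, two-sided at 0.05 and ignoring clustering within dyads, for assumed rates:

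| Assumed rates | 54 per arm | 38 per arm |
|---|---|---|
| 5% vs 15% | 0.41 | 0.30 |
| 10% vs 30% | 0.75 | 0.59 |
| 5% vs 25% | 0.84 | 0.69 |

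Only large differences would be detectable, so equal capture supports description and not a test.

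**The case against.** The strongest reply is that safety is not a listed outcome and no between-arm analysis of harms is planned. On this view the log is participant monitoring for women who are given a prescribed programme. That is correct, and it means that no planned analysis is invalid. It does not remove the gap in harms data for the women who exercise without professional guidance.

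A reader might infer that Match harms cannot be recorded at all and that Match will show zero events by construction. The article does not support this. The escalation sentence is not limited to one arm, so an event that a Match woman reports unprompted has somewhere to go. Health care use, loss of work and HRQOL (including bodily pain and pain/discomfort) are collected in both arms and could reflect consequential harm indirectly. The health care questionnaire is in a supplementary file not shown here, so it is unknown whether it asks the reason for a visit. What stands is that no systematic capture is described for Match.

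A reader might also infer that the blinding fails. That too goes beyond the text. The blinding sentence can be read as applying to data analysis. An event report reveals the allocation of one dyad, not of the analysis dataset, and does not reach the statistician. The primary outcome is self-reported online by participants who know their allocation, so no route from such a report to bias in the main result is shown. The two statements need reconciling, no more.

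It could finally be said that a journal article condenses. But here the article describes harm tracking and expressly restricts it to one arm, so the point does not rest on an omitted detail.

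**Conclusion.** The point holds as a gap in harms ascertainment. Systematic tracking is described for 54 of 108 women, and for none of the 54 Match women. In MatchQEP it consists of 10 weeks of scheduled asking and 4 weeks of on-request contact. Neither arm has any described capture for the last 12 of 26 weeks. Harms under peer-only exercise would be under-recorded, and any descriptive comparison would be tilted against MatchQEP by an amount that the article does not allow one to estimate.

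The counts assume full recruitment and equal arms. The conclusion also assumes that the supplementary questionnaires contain no injury items; the article names none. The primary endpoint and its analysis are unaffected. The change is worth making now because events not asked about during the trial cannot be reliably recovered afterwards.

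**What to change.** 1. Add the same short injury and adverse-event items to the online questionnaires that both arms complete at weeks 10, 14 and 26. This also closes the week 14–26 gap.
2. Base any description of harms by arm on those items only, and state that it is descriptive.
3. Report the QEP log separately, as MatchQEP-only data.
4. Reconcile the blinding statement with "Adverse events will be reported to the Principal Investigator immediately for follow-up", for example by stating that blinding applies to the data analysis. The safety reporting route itself should stay as it is.

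The cost is a slightly longer questionnaire and an ethics amendment, with no new visits or staff and no change in sample size. The drawback is recall over 10 weeks at the first assessment, 4 at the second and up to 12 at the last (26 − 14), so minor events will be under-reported, though the same questions would be asked in both arms.
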